## 5.6 Submission of data

The Case registration card for each subject will be submitted by fax, while other case report forms are submitted to the CSPOR data center via an electronic data capture (EDC) system in this study.

Clinical investigators, clinical research coordinators, and others will submit other case report forms to the CSPOR data center for all patients registered into this study on an ongoing basis until the completion of the study. When the Clinical Research Coordinator or another person completes the case report forms, verification by a clinical investigator is required.

Types of submitted case report forms and the method and timing of distribution/submission are shown below:

| No. | Type                                                 | Method and timing of distribution                                                                   | Method and timing of submission                                                                                               |
|-----|------------------------------------------------------|-----------------------------------------------------------------------------------------------------|-------------------------------------------------------------------------------------------------------------------------------|
| 1   | Case registration card                               | Sent to participating facilities in advance.                                                        | Fax
At the time of registration, within 2 weeks before the scheduled initiation of protocol treatment.                     |
| 2   | Report of initiation of protocol treatment           | EDC                                                                                                 | EDC
Submitted within 2 weeks after the initiation of protocol treatment.                                                   |
| 3   | Progress report (Adverse events, effect measurement) | EDC                                                                                                 | EDC
Submitted within 2 months from each specified date of the 3- and 6-month surveys.                                      |
| 4   | Progress report (After-treatment)                    | EDC                                                                                                 | EDC
Submitted within 2 months from the specified date of the annual survey after the completion of the protocol treatment. |
| 5   | Progress report (Survival)                           | EDC                                                                                                 | EDC
Submitted within 2 months from the specified date of the annual survey after the completion of the protocol treatment. |
| 6   | Emergency adverse event report                       | A form provided by the hospital is also acceptable.
Sent to participating facilities in advance. | Fax
Within 72 hours after having cognizance of the incidence.                                                              |

## 5.7 Items described in reports

### (1) Case registration card

- ① Date of entry, name of facility, name of clinical investigator, patient identification number, phone number of facility, and fax number for response
- ② Age, height, and weight
- ③ Expression status of ER and PgR (J-score classification, at least 0%, 1–9%, and 10% or higher)
- ④ Inclusion criterion (Yes/no; the date of acquisition of consent; 0, 1, or 2 is selected for PS)
- ⑤ Exclusion criterion (Yes/no; confirm that all terms do not correspond)
- ⑥ Planned treatment and scheduled initiation date

### (2) Report of initiation of protocol treatment

- ① Medical history: (Of terms in 5.3.2 (1), all items except expression of hormonal receptors and expression status of HER2)
- ② Implementation state of imaging examinations before the registration: 5.3.2 (3)
- ③ Focal findings: Presence or absence of nonmeasurable lesions, descriptions of the site and measurement results of target lesions and non-target lesions.
- ④ Adverse events
- ⑤ Concomitant drugs
- ⑥ Started drugs, reasons for drug selection, and date of initiation

### (3) Progress report: During protocol treatment

At 3 and 6 months after the initiation of protocol treatment unless discontinued.

No report at 6 months is required when discontinuation of the protocol treatment is reported in the survey at 3 months.

- ① Body weight, PS
- ② Implementation state of image examinations after the initiation of protocol treatment: 5.3.4 (2) and 5.3.5 (2)
- ③ Focal findings: Descriptions of the site and measurement results for target lesions and non-target lesions.
- ④ Adverse events
- ⑤ Concomitant drugs and treatment, and reasons for implementation
- ⑥ Presence or absence of discontinuation of the protocol treatment. When the treatment is discontinued, the reasons for the discontinuation and date of discontinuation.
- ⑦ Compliance of the protocol treatment
- ⑧ Time point response

(4) Progress report: After-treatment

- ① After-treatment survey: Implementation date and type of chemotherapy

(5) Progress report: Prognosis survey

- ① Presence or absence of progression and date of confirmation  
② Date of last confirmation of survival, date and cause of death (in case of death)

(6) Emergency adverse event report

(See Appendix E)

## 5.8 Handling of data

The CSPOR data center will implement chase-up of unsubmitted data, careful examination and inquiry of submitted data, data correction based on results of the inquiry, and database management in accordance with data management plans (Standard Operating Procedure and Manual) specified separately. The CSPOR data center will prepare monitoring materials and data for statistical analysis based on the entered data.

## 5.9 Estimated enrollment and estimated study duration

(1) Estimated enrollment

200 or more (however, registration is to be continued during the registration period even if the target number is achieved)

(2) Estimated study duration

Study duration: Four years from November 2015 to October 2019

Of this period, the registration period is a year from November 2015 to October 2016, and the observation period is November 2016 to 3 years from registration of the last case

## 5.10 Method of analysis and assay

(1) Definition of population to be analyzed

The analysis set is defined as below:

Total eligible cases: "Total eligible cases" is defined as a group of patients that overlapped and error registrations are removed from patients who registered in accordance with "5.2 Registration of cases".

Total treated cases: "Total treated cases" is defined as a subgroup of patients among the total eligible cases who received scheduled treatment at least once daily.

(2) Outcome measures

Outcome measures in this study are defined as below:

① Primary outcome measures

- Clinical benefit rate (CBR)

② Secondary outcome measures

- Progression free survival (PFS)
- Overall survival (OS)
- Time to treatment failure (TTF)
- Time to chemotherapy (TTC)
- Response rate (RR)
- Health-related quality of life
- Adverse events (toxicity)

(3) Analysis plan

① Primary analyses

Whether CBR, the primary outcome measures, exceeds 30% will be examined using accurate tests based on binomial distribution and the corresponding 90% confidence interval by cohorts with the entire secondary endocrine therapy. Meanwhile, the analysis set includes all treated cases, and a significance level of 5% is set for 1-sided tests.

② Other analyses

Analysis of the interaction effect of CBR is conducted for responsiveness to the primary endocrine therapy, expression intensity of ER, and presence or absence of PgR expression for all registered cases to examine the significance of effect predictors of the secondary endocrine therapy. The following classification will be used for each factor:

A) Responsiveness to the primary endocrine therapy

- Very low sensitivity group: Recurrence at less than 2 years after the initiation of postoperative endocrine therapy, or progression at less than 3 months after the primary therapy for metastatic breast cancer [corresponding to the ‘very low’ group of Figure 1 in 4.2 (2)].
- Low sensitivity group: Recurrence at 2–5 years after the initiation of postoperative endocrine therapy, or progression at 3–9 months after the primary therapy for metastatic breast cancer [corresponding to the ‘low’ group of Figure 1 in 4.2 (2)].

B) ER expression intensity

- ER low group: ER slightly positive (J-score classification is 1–9%)

- ER high group: ER positive (J-score classification is 10% or higher)

C) Presence or absence of PgR expression

- PgR negative group: PgR negative (J-score classification is negative)
- PgR positive group: PgR positive (J-score classification is 1% or higher)

Analyses of secondary outcomes will also be conducted on a by-cohort basis. For RR defined by a 2-value endpoint response, an accurate 90% confidence interval based on point estimation and the binomial distribution is calculated. Furthermore, for PFS, OS, TTF, and TTC, which are time-to-event outcomes, a survival curve will be estimated using a Kaplan-Meier method, and 90% confidence intervals of the survival rate at each event will be calculated using Greenwood's formula. The interaction effect will be analyzed for effect predictors in the same manner as that used for the primary outcomes.

Analysis of adverse events will be performed in all treated cases. Incidence rate by types and grade will be calculated for reported adverse events.

③ Analysis of HRQoL

FACT-G, Breast, and ES, which are calculated as total scores, will be calculated for the aggregate score and subdomain scores in accordance with a scoring manual to calculate the fundamental statistics at the time of each survey for all subjects.

Furthermore, cases with decreases in scores exceeding the threshold values as compared with scores at the registration will be individually identified and the maintenance rate of QoL will be calculated using MIDs identified by scales as a meaningful threshold value of decrease of QoL score at each measurement point.

Information obtained from questions about changes will be used as subjective anchoring information required for the identification of MID during the endocrine therapy, and differences from the previously established MID will be examined.

Since it is considered that the evaluation and analysis of HRQoL have no influence on the clinical benefit rate, which is the primary outcome measures of this study, analysis will be implemented immediately after the data collection (after the collection of QoL questionnaires at 3 months for the last registered case). The results of the analysis will be published as conference presentations and papers.

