### (2) Objectives of HRQoL evaluation

The major objective of this study is to evaluate the efficacy and safety of recent endocrine therapies for breast cancer with low sensitivity to the primary endocrine therapy. The maintenance and improvement of QoL is a key objective in the treatment of metastatic breast cancer, and evaluation of QoL is essential for the evaluation of the efficacy of treatments. HRQoL is often discussed as differences and changes in scores obtained by the statistical analysis of questionnaire data. However, it is critical to understand the clinical significance of any differences and changes in such scores. Recently, the concept of minimally important difference (MID) has been emphasized as an index to understand HRQoL scores. MID represents the clinically meaningful minimum difference in the HRQoL scores, and validation of MID is indispensable for the meaningful evaluation of HRQoL in clinical cancer research.

As mentioned above, objectives of the HRQoL evaluation in this study are as below:

- ① To clarify the effect of secondary endocrine therapy on estrogen receptor-positive, HER2-negative postmenopausal metastatic breast cancer for which the primary endocrine therapy had no favorable clinical effect (low sensitivity to primary endocrine therapy) on HRQoL using HRQoL maintenance rate, which is a clinically meaningful index.

- ② To clarify the clinical significance inherent in HRQoL score values as the minimally important differences (MIDs) associated with endocrine therapy for metastatic breast cancer by focusing attention on variations in HRQoL scores obtained for subjects of this study over time.

(3) HRQoL scales

The following scales are used (Appendix F).

In addition, a questionnaire survey related to the social background and expectancy of QoL of patients, which may have an impact on subsequent HRQoL scores, will be conducted at the time of registration.

- ① (Functional Assessment of Cancer Therapy) ES (Endocrine Symptoms, 19 items) and B (Breast, 10 items) as additional QOL scales, FACT-G (General, 27 items, Japanese version), which is a scale generally used for clinical studies of cancer.
- ② Questions about changes: Used as subjective anchoring information required for identification of MIDs (minimally important differences).

(4) Survey schedule

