### 7.3 Sample size determination

This study is an observational study, in which therapy is selected based on the preferences of medical staff and patients. The study does not aim to compare different cohorts. To test the major study hypothesis, the threshold clinical benefit rate is set as 30%, and the expected clinical benefit rate is set as 50% in each cohort. Assuming the use of an accurate binomial test, it is estimated that the required number of cases is 43 under a condition of  $\alpha=0.05$  (one-tailed) and  $\beta=0.2$ . Assuming a dropout rate of about 10%, the target sample size estimated to be required for each cohort was set at 50. This study is an observational study, and cases will not always be evenly distributed to each cohort. However, it is needed to set the sample size corresponding to the 4 groups at a maximum [(4) Selection of drugs]. Therefore, a target case quantity of at least 200 was set. Meanwhile, registration will continue until all 4 groups achieve the target number of 50 cases per group within the time frame set for registration, even after a total registration number of 200 cases is achieved.

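### The HRQoL maintenance rule flags only decreases beyond the MID, so a fall of exactly the MID, which the protocol defines as meaningful, counts as maintained

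*Protocol*

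**What the plan says.** Protocol 5.5 (2), on the objectives of the HRQoL evaluation, states that "MID represents the clinically meaningful minimum difference in the HRQoL scores". Its objective ① is to describe the effect of secondary endocrine therapy on HRQoL "using HRQoL maintenance rate, which is a clinically meaningful index". Objective ② is to establish MIDs for endocrine therapy in metastatic breast cancer.

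Protocol 5.10 (3) ③ turns this into an analysis rule. It says that "cases with decreases in scores exceeding the threshold values as compared with scores at the registration will be individually identified", and that the maintenance rate is calculated "using MIDs identified by scales as a meaningful threshold value of decrease of QoL score at each measurement point". It adds that the questions about changes will serve as anchors for an MID in this setting, and that "differences from the previously established MID will be examined". Scores "will be calculated for the aggregate score and subdomain scores in accordance with a scoring manual".

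The protocol gives no numerical MID, no standard deviation of change and no score step. It does not write the maintenance rate as a formula.

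**The concern.** The definition and the rule disagree at one point: a fall of exactly the MID. Under 5.5 (2) such a fall is the smallest one that matters to a patient. Under 5.10 (3) ③ as worded it does not exceed the threshold, so the patient is left among those whose quality of life is maintained.

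The maintenance rate is the index named for HRQoL objective ①, and HRQoL is a listed secondary outcome. A mismatch at the boundary works in one direction only, towards a more favourable rate. It would apply to every total and subdomain score for which the rate is calculated, at both post-baseline surveys. Section 5.10 (3) ③ also schedules the HRQoL analysis and its publication soon after the last 3-month questionnaires are in, so the rule needs to be settled before then.

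The missing MID values are not the complaint; those may properly stand in an analysis plan or scoring manual. The complaint is that the protocol does state the direction of the inequality, and that direction does not fit its own definition.

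**Working it through.** **Step 1: the two sections side by side.** Let D be the fall in score from registration to a survey, and M the MID of that scale. Maintained is taken as the complement of an identified decrease, which is implied but not written out.

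- Definition in 5.5 (2): M is the smallest meaningful difference, so a fall is meaningful when D ≥ M, and maintained means D < M.
- Rule in 5.10 (3) ③ as worded: a decrease is identified when D > M, so maintained means D ≤ M.

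The two rates differ by P(D ≤ M) − P(D < M) = P(D = M). A probability cannot be negative, so the rate as worded is equal to or higher than the rate under the definition, never lower.

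**Step 2: what the document fixes.** It states no maintenance rate, so there is no figure to reproduce. P(D = M) depends on three quantities that it does not give: M, the spread of the change, and the score step.

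**Step 3: when the effect is zero.** If M is not an attainable change, for example 4.5 on a scale that moves in whole points, then P(D = M) = 0 and the two rules give identical results.

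**Step 4: illustration under assumptions.** Assume that the change is Normal with mean μ and standard deviation SD, rounded to whole points, and that M is a whole number. Then

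P(D = M) = Φ((−M + 0.5 − μ)/SD) − Φ((−M − 0.5 − μ)/SD).

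Example with μ = 0, SD 4, M 2: Φ(−0.375) − Φ(−0.625) = 0.354 − 0.266 = 0.088. Maintained as worded is 1 − 0.266 = 73.4%; under the definition it is 1 − 0.354 = 64.6%.

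| μ | SD | M | Difference (percentage points) |
|---|---|---|---|
| 0 | 3 | 2 | 10.6 |
| −2 | 4 | 2 | 9.9 |
| 0 | 4 | 2 | 8.8 |
| 0 | 5 | 3 | 6.7 |
| 0 | 8 | 5 | 4.1 |
| 0 | 10 | 5 | 3.5 (70.9% against 67.4%) |
| 0 | 12 | 7 | 2.8 |
| 0 | 15 | 8 | 2.3 |
| 0 | 4 | 8 | 1.4 |

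These combinations span about 1 to 11 points. The extreme corners of the same assumed ranges fall slightly outside: SD 3 with M 8 and μ = 0 gives Φ(−2.500) − Φ(−2.833) = 0.4 points, and SD 3 with M 2 and μ = −2 gives Φ(0.167) − Φ(−0.167) = 13.2 points. For SD 10 to 15, with M of 2, 5 or 8 and μ of 0 or −2, the range is 2.3 to 4.0 points.

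In patients, if all 200 planned subjects answered, 3.5 points would be 200 × 0.035 = 7 patients and 8.8 points about 18.

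**The case against.** The best defence is that the word was never meant as a strict inequality. The protocol is a translation and moves between the two forms elsewhere. Its hypothesis for the clinical benefit rate is worded inclusively at 30% in 0.3, 4.3 and 7.2, while the analysis in 5.10 (3) ① asks whether the rate lies above 30%. Calling the MID a meaningful threshold also fits a reading in which reaching it is enough. How ties at a cutoff are handled is ordinary analysis-plan detail, and no analysis plan is at hand.

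Loose wording is a plausible explanation, and this part stands as such. It does not make the written rule agree with 5.5 (2), and an analysis plan that follows 5.10 (3) ③ word for word would carry the mismatch forward. The protocol can be inclusive when it wants to be: the partial response and progression limits in 3.8 (4) are both stated that way. If the intended rule is inclusive, the same edit puts it on paper.

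The objection to any claim about size stands in full. A reader might infer that the maintenance rate is overstated, that exact ties are common, or that the shorter scales have MIDs of only 2 to 3 points. The protocol supports none of these. It leaves scoring to a manual, gives no MID, and plans to derive one from anchor questions, which need not yield a whole number.

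It is also true that no target, test or success criterion is attached to the maintenance rate, and that 7.3 disclaims comparison between cohorts.

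**Conclusion.** The point holds as an inconsistency between a stated rule and the protocol's own definition. Followed literally, 5.10 (3) ③ counts a fall of exactly the MID as maintained, and any resulting error can only raise the rate.

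Whether the rate would in fact be raised, and by how much, cannot be settled from the document. The effect is nil if the MID is unattainable as a change score. Otherwise it is of the order of 1 to 11 percentage points in the cases worked, all of which rest on assumed whole-point scores, whole-number MIDs and a Normal change.

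This is a minor point on a secondary, descriptive outcome. It has no bearing on the clinical benefit rate, its test or the sample size.

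**What to change.** In 5.10 (3) ③, change the condition for an identified case from a decrease exceeding the threshold to a decrease equal to or greater than the MID. Nothing need be added about timing: the existing reference to each measurement point, with the schedule in 5.5 (4), already covers 1 and 3 months.

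The cost is one phrase. No new data, procedure or sample size is needed. The reported maintenance rate stays the same or becomes somewhat less favourable. The edit is best made before the HRQoL data are analysed, so that the boundary is not chosen with the results in view.

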## 6 Subject selection policy

### 6.1 Definition of the subject of this study

Although there is no existing consensus about how to define "ER-positive, HER2-negative postmenopausal metastatic breast cancer with low sensitivity to the primary endocrine therapy", a definition is established as below in this study:

- Cases that are continuing postoperative adjunct endocrine therapy and experienced recurrence within 5 years after the initiation of the therapy.
- Cases that experienced disease progression within 9 months after the initiation of the primary endocrine therapy for metastatic breast cancer.

These correspond to the "very low" and "low" groups described in Figure 1 in 4.2 (2).

Cases that fit the definition of the above-mentioned clinical course are called "breast cancer with low sensitivity to the primary endocrine therapy" in this study.

### 6.2 Inclusion criteria

Cases that satisfy all of the following conditions are included in this study as subjects.

- (1) A patient with estrogen receptor (ER) positiveNote 2 postmenopausalNote 3 breast cancer who is histologically diagnosed as breast cancerNote 1.

Note 1: No distinction is made according to the tissue subtype of cancer.

Note 2: Determination of ER is based on the determination of the primary focus of the breast in accordance with the definition of ER positive that is detailed in section 3.6. In this regard, a case in which evaluation of the primary focus is difficult and which is determined as ER positive based on evaluation of a metastatic lesion can be registered. Furthermore, when the results of evaluation differ between the primary focus and metastatic lesion, the result of the primary focus will be considered for the evaluation of ER expression.

Note 3: At least 1 of the following conditions regarding menopause should be satisfied.

- ① Aged 60 years or older
- ② Younger than 60 years and absence of menstruation for the past 1 year or longer (without hysterectomy)
- ③ Had bilateral oophorectomy

When the presence or absence of menopause of the subject is unclear, FSH and plasma estradiol levels will be measured to confirm whether these are at the after menopausal level as defined by the criteria of each facility.

- (2) Diagnosis of breast cancer corresponds to either of the following. No distinction is made according to the presence or absence of measurable lesions.

- ① Stage IV breast cancer associated with distant metastasis that cannot be a candidate for surgery at the first visit.  
(See 3.3 Classification of clinical stages)
  - ② Breast cancer associated with progression or recurrence caused by distant metastasis after initial treatment (after surgery and treatment before or after the surgery) for breast cancer aiming at curing. However, local recurrence for which radical excision is applicable (this represents the chest wall surrounded by the lower edge of the clavicle as the upper limit of surgical site, the costal arch as the lower limit, the midline of the sternum as interior limit, and the anterior edge of the latissimus dorsi muscle as the outer limit) is excluded.
- (3) Endocrine therapy for metastatic breast cancer is planned.
- (4) Performance status (PS) of ECOG is 0 or 1 Note 4.  
(See 3.5 Evaluation of Performance Status (PS))
- Note 4: A case determined as PS 2 because of decreased activity due to bone metastasis will be considered as eligible.
- (5) Previous endocrine therapy for breast cancer corresponds to either of the following. No distinction is made according to the type of endocrine therapeutic medicines used.
- ① A case that has continuously received endocrine therapeutic medicines as a postoperative adjunct therapy and in which recurrence occurred within 5 years after the initiation of the endocrine therapy.
  - ② A case that received endocrine therapy as the primary treatment for metastatic breast cancer Note 5 and in which progression of the disease occurred within 9 months after the initiation of the endocrine therapy.
- Note 5: A case that received postoperative endocrine therapy for at least 5 years and had metastasis 5 or more years after the initiation of the endocrine therapy will not be included. In addition, a case that discontinued postoperative endocrine therapy within 5 years for any reason and then had metastasis and recurrence will also not be included.
- (6) Previous chemotherapy for breast cancer corresponds to either of the following:
- ① No previous chemotherapy was administered.
  - ② When chemotherapy was administered as a preoperative or postoperative adjunct therapy, it has been at least 6 months (168 days, 24 weeks) since the final day of administration.
- (7) Previous radiotherapy for breast cancer corresponds to the following:
- ① It has been at least 14 days after the final day of radiotherapy administration.

- (8) Agreement about the participation in the study will be obtained from the subject him/herself using the consent form (Appendix G).

